### Study population, eligibility and recruitment

DTG RESIST enrols adults and adolescents (age 10–19 years) living with HIV who have been on dolutegravir for at least 3 months and experience virological failure during routine care, defined as a single or, if available, a confirmed VL >1000 copies/mL on any dolutegravir-based combination ART regimen (figure 2). At enrolment, written informed consent is obtained from the participant or the parents or caretaker, as per local regulations. Key clinical and demographic data are collected using the Research Electronic Data Capture system.^20^ The DTG RESIST data will be combined with the clinical and epidemiological data prospectively collected within IeDEA.^17^,^19^

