### Outcomes and statistical analyses

We define two analysis populations to address aim 1 and aim 2: (1) all individuals who experienced virological failure on a dolutegravir-based first-line, second-line or third-line regimen in one of the participating cohorts and (2) all who started ART on a dolutegravir-based regimen or switched to such a regimen and were at risk of developing virological failure (the source population for (1)). The outcome of interest in population (1) will be any InSTI DRMs whereas in (2), it will be virological failure as defined above.

We will analyse population (1) using random-intercept logistic regression and population (2) using parametric survival models,^31^ stratified by treatment programme or country to account for heterogeneity across sites. We will measure the time from the date of switching to DTG-based ART (or from 6 months after initiating DTG-based first-line ART) to the earliest onset of virological failure, date of death or date of last follow-up visit. Exposure variables include age, sex, type of dolutegravir-based ART (initiated first line, switched to first line, second line or third line), previous exposure to InSTI drugs, pre-existing resistance mutations (from HIV-1 genotypes or predicted by the approach described below), advanced disease (as indexed by CD4 count <200 cells/µL), exposure to rifampicin, a history of ART interruptions and VL monitoring coverage and frequency (using approaches used in previous analyses^32 33^). We will follow recommendations on the conduct and reporting of prognostic research, including the choice of variables for inclusion in models and the handling of continuous variables and non-linear relationships.^34^ Missing values will be imputed using multiple imputations, assuming data are missing at random.^35^

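### Follow-up in the survival analysis does not end when dolutegravir is stopped, although the outcome is failure on dolutegravir; rates are diluted, and hazard ratios are biased if stopping differs by exposure

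*Protocol article*

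**What the plan says.** The section on study population, eligibility and recruitment describes virological failure as "defined as a single or, if available, a confirmed VL >1000 copies/mL on any dolutegravir-based combination ART regimen". The section on outcomes and statistical analyses then sets up two populations.

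- Population (1) is "all individuals who experienced virological failure on a dolutegravir-based first-line, second-line or third-line regimen in one of the participating cohorts".
- Population (2) is everyone who started or switched to such a regimen, and is described as the source of population (1). For its outcome the article says "it will be virological failure as defined above".

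The analysis is of "population (2) using parametric survival models", stratified by programme or country. On the clock, the article says: "We will measure the time from the date of switching to DTG-based ART (or from 6 months after initiating DTG-based first-line ART"). Time then runs "to the earliest onset of virological failure, date of death or date of last follow-up visit". Stopping or switching away from dolutegravir is not in that list. A history of ART interruptions appears only as an exposure variable, not as a pause or end of time at risk. The abstract gives a shorter definition of failure for population (2): the same viral load threshold, without the condition of being on dolutegravir.

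**The concern.** The event can happen only on dolutegravir, but the clock keeps running off it. A person who changes to another regimen contributes person-time until the last visit without being able to contribute an event. The estimated failure rate is then lower than the rate on dolutegravir.

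For risk factors, which are the purpose of aim 2, the effect depends on who stops. The group that stops more often has its rate pulled down further, so a factor related to stopping can look protective, harmful, weaker or stronger for reasons unrelated to failure on the drug.

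If viral loads after stopping were counted instead, failures on other regimens would enter an outcome defined on dolutegravir, and population (2) would no longer be simply the source of the failures in population (1).

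**Working it through.** The article states no hazard ratio, stopping rate or person-time for this analysis, so there is no figure to reproduce. The check is the fit of the rule to the outcome, followed by an illustration of size.

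**Fit of the rule**

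| Element | What the article fixes |
|---|---|
| Event | viral load above 1000 copies/mL, "on any dolutegravir-based combination ART regimen" |
| Link between populations | (2) is the source of the on-dolutegravir failures in (1) |
| End of time | failure, death or last visit |
| Leaving dolutegravir | not an end of time, a competing event or a time-varying exposure |

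**Simple illustration**

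Assume that a share s0 of the reference group and s1 of the exposed group stop, on average halfway through follow-up, and that failures after stopping do not count. On-drug time is then a fraction 1 − 0.5s of the time counted, so

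observed HR = true HR × (1 − 0.5·s1) / (1 − 0.5·s0).

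- s0 = 5%, s1 = 20%, true HR 1.00: 0.90 / 0.975 = 0.92.
- s0 = 5%, s1 = 30%, true HR 1.00: 0.85 / 0.975 = 0.87.
- s0 = 20%, s1 = 5%, true HR 1.30: 1.30 × 0.975 / 0.90 = 1.41.
- s0 = s1: the ratio cancels. The absolute rate is still too low, for example by 10% when 20% stop (1 − 0.5 × 0.20 = 0.90).

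**Check with exponential times**

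The failure hazard is λ = −ln(1 − r)/2, with the 2-year failure risks r = 10%, 20% and 30% that the sample size section assumes for first-, second- and third-line ART. Follow-up is T = 2 years. Stopping is an independent exponential event with hazard μ at assumed yearly risks. With h = λ + μ:

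- on-drug time = (1 − e^(−hT))/h
- on-drug failures = λ × on-drug time
- time as the article counts it = T − (λ/h) × (T − on-drug time)

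Worked case: r = 10%, so λ = 0.0527, with the same failure hazard in both groups (true HR 1.00).

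- Reference group, 5% stopping per year (μ = 0.0513): on-drug time 1.806, failures 0.0951, counted time 1.902, rate 0.0500.
- Exposed group, 20% stopping per year (μ = 0.2231): on-drug time 1.537, failures 0.0810, counted time 1.912, rate 0.0424.
- Ratio: 0.0424 / 0.0500 = 0.85. A simulation of this case gave 0.84 as written and 1.00 with on-drug time only.

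Across the three failure risks, with 5% per year stopping in the reference group:

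| Exposed group stops per year | True HR 1.00 reads | True HR 2.00 reads |
|---|---|---|
| 5% (equal) | 1.00 | 1.99 to 2.00 |
| 10% | 0.95 | 1.88 to 1.89 |
| 20% | 0.84 to 0.85 | 1.67 to 1.69 |
| 30% | 0.74 to 0.75 | 1.47 to 1.49 |

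At the reference failure hazards, counted time exceeds on-drug time by about 5% at 5% stopping per year, 11% at 10% and 24% to 25% at 20%.

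If failures after stopping are counted (r = 10%, 5% versus 10% to 30% stopping per year), a true HR of 1.00 reads 0.98 to 0.88 when the off-drug failure hazard is half the on-drug one, and 1.04 to 1.22 when it is twice as high.

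**The case against.** The strongest reply is that the abstract defines failure for population (2) by viral load alone. On that wording a person who has left dolutegravir can still have the event, and the analysis follows people from starting or switching whatever they take later. That is a recognised target, and it fits the article's framing as prognostic research. Keeping people who stop in the risk set can also be read as a subdistribution-type analysis. This part stands: a reader might infer that the stated rule gives a wrong rate on any reading, and the documents do not support that. They do not support the alternatives as the plan's intention either. The methods text refers back to the on-dolutegravir definition and makes population (2) the source of on-dolutegravir failures. No subdistribution analysis is announced, and time ends at death, so that approach would not be applied consistently.

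A second reply is that censoring rules belong in the full protocol or analysis plan. That would answer silence. Here the article gives an explicit list of end points, and the list does not match its own outcome.

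A third reply is that nothing in the article shows that stopping is common or differs by exposure, and that it describes dolutegravir as recommended across treatment lines, with fairly uniform treatment options. This stands as a limit on size.

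**Conclusion.** The point holds as a mismatch between a stated follow-up rule and the outcome it serves. Absolute failure rates on dolutegravir are diluted to the extent that people stop. Hazard ratios are biased only if stopping differs by exposure.

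Two stronger conclusions are tempting and should be resisted. One is that hazard ratios are pulled towards or past 1. That holds only if the true ratio is at least 1 and the exposed group stops more often; with the stopping pattern reversed, 1.30 becomes 1.41. The other is that particular factors, such as rifampicin exposure or later-line ART, will be biased. The article does not say that these change stopping.

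All sizes rest on assumed stopping rates, on stopping that is independent of failure and, in the simple formula, on stopping halfway through follow-up on average. They show that the effect could matter, not that it will. The change is worth making because it is cheap and removes the inconsistency.

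**What to change.** In the outcomes and statistical analyses section, add the date dolutegravir is discontinued as an end of follow-up for population (2), so that only person-time and viral loads on dolutegravir count. Align the abstract's definition of failure with the one in the eligibility section.

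Ending time at discontinuation recovers the on-drug hazard only if stopping is unrelated to the risk of failure. People may stop for reasons linked to that risk, and the discussion reports no harmonised adherence data with which to adjust. Add a sensitivity analysis that treats discontinuation as a competing event, or that follows people regardless of later regimen, and say which question each analysis answers.

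The cost is a clause of wording, one added analysis and regimen stop dates from the linked IeDEA cohort data. Recruitment and sampling are unaffected. The downsides are slightly less person-time and possible informative censoring.

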## Study aims and hypotheses

The prospective part of DTG RESIST has three aims:

In aim 1, we examine viral sequences to determine the prevalence and patterns of dolutegravir resistance in adults and adolescents living with HIV-1.In aim 2, we combine the HIV drug resistance data from aim 1 with clinical and programmatic data collected within the International epidemiology Databases to Evaluate AIDS (IeDEA) network to explore the factors associated with emergent dolutegravir resistance.In aim 3, we characterise the phenotypic effect of novel drug resistance mutations (DRMs) or novel combinations of mutations and explore the mutational pathways of dolutegravir resistance across HIV-1 subtypes.

We hypothesise that the prevalence and spectrum of InSTI DRMs will differ by HIV-1 subtype and by treatment context (aim 1); that NRTI resistance, previous exposure to InSTI drugs, male sex, younger age, second-line or third-line ART or advanced disease, exposure to rifampicin and lack of routine VL monitoring are risk factors for virological failure and the development of dolutegravir resistance (aim 2); and that HIV genotypes from patients experiencing failure of dolutegravir-based ART are associated with phenotypic resistance. We further hypothesise that these mutations develop along pathways specific to each HIV-1 subtype and, in combination, may compensate for the fitness costs of resistance mutations, that is, restore replication capacity compared with single mutations (aim 3).

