We will explore using conjunctive Bayesian network models to assess the mutational pathways of DTG resistance (aim 3).^36^,^38^ The order of mutation accumulation and interdependence between mutations (ie, whether the acquisition of one mutation is less or more likely in the presence of other mutations) will be inferred from the co-occurrence patterns of mutations. We will learn these models for each subtype separately to identify subtype-specific mutational pathways. In exploratory analyses, we will search for novel resistance mutations that may mediate treatment failure and assess the impact of previously proposed mutations, such as mutations outside the HIV-1 integrase.^39 40^ We will combine the genotype data generated in aim 1 with viral whole genome sequences from phylogenetically matched controls from the Los Alamos HIV sequence database. In this pooled dataset, we will use GWAS methodology (as implemented in the PLINK software^41^) to identify the amino-acid mutations associated with failure.

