DTG RESIST will generate whole HIV-1 genomes and develop robust laboratory procedures to amplify, sequence and assemble the genomes from the diverse set of HIV-1 strains obtained in the multiregional network.^27^ The spectrum of dolutegravir-selected mutations and their effects on phenotypic susceptibility in non-B subtypes is yet to be fully characterised. HIV-1 main group (group M) has diversified into nine subtypes (A–D, D–H and J–K), six subsubtypes (A1–A4 and F1–F2), multiple CRFs and thousands of unique recombinant forms.^58 59^ Most PWH are infected with non-B subtypes, but much of the evidence about ART outcomes and HIVDR is based on subtype B viruses from Europe and North America. HIV-1 subtype could influence treatment outcomes and the emergence of drug resistance.^60^,^62^ Finally, phenotypic testing of non-B subtype viruses with major InSTI resistance mutations and GWAS to explore the effect of mutations outside of the integrase will likely provide new insights into the relevant drug resistance pathways. Bayesian evolutionary models of accumulating mutations will be used to predict the expected genotype at treatment failure.^36^

There are also limitations to the approach. An important weakness is the lack of genotypic resistance data from before dolutegravir treatment for most participants. We considered collecting and biobanking samples from all people starting dolutegravir-based ART and then having paired samples from pretreatment and at the time of virological failure. However, this was not deemed feasible at most IeDEA sites. We will explore whether these missing baseline genotypes can be imputed by adapting models to predict expected resistance genotypes based on treatment and clinical history. Other challenges include the lack of harmonised data on adherence. There is uncertainty about the distribution of HIV-1 subtypes across sites, and the statistical power of the analyses of patterns and risk factors for dolutegravir resistance will be limited. We will consider pooling our data with those from other related studies to address these issues.^15^ The results of the GWAS and Bayesian network analyses may be subject to overinterpretation due to strong model assumptions and limited sample size. To avoid this, we will qualify these as preliminary and hypothesis-generating studies requiring validation.

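### The conjunctive Bayesian network named for aim 3 cannot show that one mutation makes another less likely, although the plan lists this among the things to be inferred

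*Protocol article*

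**What the plan says.** Under Outcomes and statistical analyses, the protocol article states: "We will explore using conjunctive Bayesian network models to assess the mutational pathways of DTG resistance". The next sentence sets the target: "The order of mutation accumulation and interdependence between mutations", the latter explained as "whether the acquisition of one mutation is less or more likely in the presence of other mutations". Both are to be learned from how often mutations are seen together. The plan continues: "We will learn these models for each subtype separately to identify subtype-specific mutational pathways". No other model is named for dependence between mutations. The genome-wide association analysis in the same section compares failures with database controls, which is a different question.

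The hypothesis served is in Study aims and hypotheses: "We further hypothesise that these mutations develop along pathways specific to each HIV-1 subtype". The Discussion adds a use for the models: "Bayesian evolutionary models of accumulating mutations will be used to predict the expected genotype at treatment failure". It also warns that the network results rest on strong assumptions and small numbers, and it labels them tentative and in need of validation.

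**The concern.** The stated question has two directions, but the named model can answer in only one. A conjunctive network holds a mutation's rate at zero until all its parents are present and at a positive constant afterwards. It has no term by which one mutation slows or excludes another, and no rule by which a mutation may follow either of two parents.

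Two consequences follow. First, a fitted network with no negative link says nothing about inhibition, yet a reader told that the analysis looks for *less or more likely* could take it as evidence that there is none. Second, if resistance arises by alternative routes that share a later mutation, the nearest conjunctive network may give a misleading order. Such an error could carry into subtype-specific pathways and into the predicted genotype at failure.

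**Working it through.** **Inputs.** From Sample size and power calculations: about 1500 failures, 84 to 157 carriers of InSTI DRMs, and 250 per subtype in the worked example. The plan gives no mutation rates, inhibition strengths or sampling times, so all of these below are assumptions. There is no stated figure to reproduce.

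**1. Sign of the association.** In the model, the time of mutation j is the latest time among its parents plus an independent waiting time. Presence at sampling is then a decreasing function of the waiting times and an increasing function of sampling time. Functions that are monotone in the same direction in independent variables have non-negative covariance (the Harris inequality), for any network and any rates. For two mutations in discrete form with A before B, P(A) = a and P(B) = P(both) = ab, so the covariance is ab(1 − a) ≥ 0. Independent symmetric observation error e below 0.5 multiplies the covariance by (1 − 2e)², which cannot change its sign.

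Numerical check over all 219 partial orders on four mutations, 60 random parameter sets each: the smallest covariance was 8.7e-06 in continuous time and zero to rounding in discrete form.

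**2. What a true inhibition looks like.** Assume rate 0.5 for A and for B, cut to 0.5 × 0.05 = 0.025 once the other is present, and exponential sampling at rate 1.
- P(neither) = 1/(1 + 1) = 0.500
- P(A only) = P(B only) = 0.5 × 0.5/(1 + 0.025) = 0.244
- P(both) = 1 − 0.500 − 2 × 0.2439 = 0.012
- Odds ratio = 0.500 × 0.0122/0.2439² = 0.10

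Fitted networks, with an error rate allowed, gave odds ratios of 1.00 to 1.02 and P(both) = 0.066. That is the product of the margins: (0.2439 + 0.0122)² = 0.066. Strong inhibition is returned as independence.

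**3. Either/or routes.** Let C follow A or B. Take rate 0.0585 each for A and B, without inhibition, and N = 1500.
- Carriers: 1500 × 0.117/1.117 = 157
- A: 1500 × 0.0585/1.0585 = 83, and the same for B
- Both A and B: 2 × 82.9 − 157.1 = 9
- C at rate 3: 157 × 3/(1 + 3) = 118; C at rate 1: 157 × 1/2 = 79

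A network requiring both A and B before C can explain C in only about 9 sequences. When C is fast it is commoner than A or B, so placing C first fits better. When C is slow that advantage is gone.

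Maximum-likelihood search over all 19 partial orders on three mutations gave:

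| Data | C rate | Discrete: C placed first | Continuous time: C placed first |
|---|---|---|---|
| Exact distributions | 1 | 2 of 4 settings | 0 of 4 |
| Exact distributions | 3 or 10 | 8 of 8 | 7 of 8 (the other gave a mixed order) |
| N = 1500, 157 or 84 carriers | 3 or 10 | 25/25 runs in every setting | 25/25 in every setting |
| N = 250, 26 carriers | 3 or 10 | 25/25 in every setting | 24/25 or 25/25 |

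The N = 250 row is closest to the plan, which fits each subtype separately.

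**4. What the data can say directly.** If A and B are independent, the chance of seeing no double carrier is roughly (1 − m/N)^m for m carriers of each.
- N = 600, m = 50: (1 − 0.0833)^50 = 0.013
- N = 1500, m = 60: (0.96)^60 = 0.086
- N = 250, 26 carriers split 13 and 13: (0.948)^13 = 0.50

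Simulated power of a one-sided Fisher test under full exclusion agrees: 97% in the first case and 14% in the second.

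**The case against.** The plan only proposes to explore these models, and the Discussion already calls the results tentative and cites strong assumptions. No primary outcome, sample size or analysis for aims 1 and 2 depends on them. The two-sided phrase may be a loose gloss on interdependence. The hypothesis on compensation concerns positive dependence, which the model can hold. The cited method papers are not at hand, so an extension may be meant.

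This lowers the weight of the point but does not remove it. The caveat neither says that negative dependence is unrepresentable nor withdraws it as a target, and the text names only the conjunctive model. If an extension is intended, naming it settles the matter.

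Three stronger readings are tempting and are not supported.
- *The order will come out reversed.* This needs alternative routes sharing a fast later mutation, which the plan does not describe. In five other assumed settings the rate ran from 28% to 97%.
- *More data make it worse.* The only two of those settings that differ in N alone gave 55% (N = 600) and 48% (N = 250) over 60 runs each. The standard error of the difference is √(0.55 × 0.45/60 + 0.48 × 0.52/60) = 9 points. N = 1500 gave both the highest and the lowest rate.
- *A mutual hazard network should replace it because it finds inhibition every time.* It did give a negative A–B effect in all runs with true exclusion. Refitted to data with no A–B interaction, it still gave one in 70–100% of runs (65–100% in a second implementation), and the right order in only 35–100%.

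**Conclusion.** The mismatch holds: the plan promises an inference that the standard form of the named model cannot make. The sign result follows from the model's definition and needs no assumption about rates. The order result is conditional: the model cannot hold either/or routes, and it can place a shared later mutation first when that mutation follows quickly, but often does not when it follows slowly. A reader might infer that any pathway reported will be an artefact; the documents give no mutation rates from which to conclude that. Because the analysis is exploratory and labelled so, this is a correction of scope and wording plus a small added analysis.

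**What to change.** In Outcomes and statistical analyses:
1. Limit the conjunctive network to a hypothesis-generating description of order and positive dependence. State that it cannot represent inhibition or a mutation that follows either of two alternatives.
2. Assess dependence of either sign directly, for example with subtype-stratified exact odds ratios and intervals. Use all sequenced failures, including those without InSTI DRMs, because restricting to carriers itself induces negative association. If this is not wanted, delete *less* from the objective.
3. Optionally add a free-sign model, such as a penalised mutual hazard network, as a sensitivity analysis. Read its negative effects only with intervals checked against a simulated no-interaction null.

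The cost is a few sentences and a little more analysis, with no new data or participants. The fix does not create power: with 84 to 157 carriers split over subtypes, intervals will be wide and exclusion between rare mutations will stay inconclusive. The gain is that the report will show that uncertainty instead of returning independence by construction.
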